#### Genetic instrument selection

The UK Biobank protein expression GWAS summary statistics^43^ will be used to select SNPs associated with circulating PD-1 or PD-L1 concentration. The genomic regions of the genes encoding PD-1 (*PDCD1*, chr2:241849884–241858894 in human genome build 38 (hg38)) and PD-L1 (*CD274*, chr9:5450503-5470566 in hg38) will be used to define *cis* and *trans* genetic instruments based on different window sizes.

To minimise vulnerability to horizontal pleiotropy, only SNPs within and in proximity to the gene encoding the target protein, known as *cis* SNPs, will be included in genetic instrument sets for the main analyses.^51^
*Cis* instruments to proxy both proteins will be constructed in PLINK version 1.9^52 53^ using SNPs in or within 500 kilobases (kb) from *PDCD1* or *CD274* that are associated with expression of these proteins (p < 5×10^-6^) at linkage disequilibrium (LD) r^2^ < 0.30 (based on clumping with a random sample of 10 000 European participants from the UK Biobank).^5 51 54^

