#### Estimator

Where the genetic instrument consists of one SNP, the Wald ratio will be used to assess the association between a protein instrumented by this SNP and cancer survival.^6 40 55^ Where a genetic instrument consists of two or more SNPs, the inverse-variance weighted method will instead be used to investigate the association between a protein instrumented by these SNPs and cancer survival.^6 40 55^ Any LD between SNPs included in an instrument will be accounted for in analysis using a SNP correlation matrix based on a random sample of 10 000 participants of European ancestry from the UK Biobank.^42 54 56^ Heterogeneity of MR results across independent SNPs included in the genetic instrument sets will be assessed using Cochran’s Q tests and MR results will be compared across each SNP in the instrument by visual inspection.^36 40 57^

The protein expression GWAS included age, age², sex, age–sex interaction terms, protein expression level measurement batch, UK Biobank centre, genotyping array, the first 20 principal components (PCs) of genetic ancestry, and duration between blood sample collection and protein expression measurement as covariates, in addition to preselection status of the participants for the replication cohort.^43^

Aside from the breast cancer GWAS which did not adjust for any covariates, the cancer site-specific GWAS were all adjusted for genetic PCs (although for different numbers of PCs).^44–48^ The colorectal cancer survival GWAS additionally adjusted for age at diagnosis, sex, genotyping platform and study where the data originated from.^45^ The head and neck cancer GWAS will be additionally adjusted for age, sex, stage at diagnosis (stratified as early or late stage) and cancer subtype. The lung cancer survival GWAS also adjusted for age and sex, and separated participants into early-stage (stage I–II), late-stage (stage III–IV) and all stage analyses (unpublished). The melanoma survival GWAS included age and sex as covariates in addition to genotyping batch for one cohort.^46^ For the ovarian cancer survival GWAS, the primary study, residual disease, tumour stage, histology, tumour grade and age were also adjusted for.^47^ The prostate cancer survival GWAS additionally included age, diagnostic prostate-specific antigen level and Gleason score as covariates.^48^

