#### Power

Using the UK Biobank protein expression GWAS,^43^ the lead *cis* SNP for *PDCD1* (variant located at chr2:242801752 in human genome build 37 (hg37) with CG (A0) and C (A1) alleles) explained approximately 2.97% of the variation in circulating PD-1 expression level while the lead *cis* SNP for *CD274* (rs822341) explained approximately 4.17% of the variation in PD-L1 expression level.

Across all seven cancer types, there is an estimated power of 80% to detect HRs of at least ≥1.63 or ≤ 0.62 per unit decrease in normalised protein expression levels (alpha set to 5%) (table 3).

**Table 3 T3:** Estimated number of participants (N), death proportion, median survival, and HR per SD decrease detectable with 80% power for each cancer site

Cancer	N	Death proportion	Median survival (months)	HRs detectable at estimated 80% power	
				PD-1	PD-L1
Breast	93 869	0.083	64.8^71^	HR ≥ 1.21 HR ≤ 0.83	HR ≥ 1.17 HR ≤ 0.86
Colorectal	19 154	0.238	38.4^71^	HR ≥ 1.28 HR ≤ 0.78	HR ≥ 1.22 HR ≤ 0.82
Head and neck	10 196	0.331*	54.3^72^	HR ≥ 1.34 HR ≤ 0.75	HR ≥ 1.26 HR ≤ 0.79
Lung	8670	0.599*	3.6^71^	HR ≥ 1.27 HR ≤ 0.79	HR ≥ 1.21 HR ≤ 0.83
Melanoma	11 201	0.103	53.4^73^	HR ≥ 1.63 HR ≤ 0.62	HR ≥ 1.50 HR ≤ 0.67
Ovarian	3395	0.552*	30.1^74^	HR ≥ 1.48 HR ≤ 0.68	HR ≥ 1.37 HR ≤ 0.73
Prostate	24 023	0.146	62.4^71^	HR ≥ 1.33 HR ≤ 0.75	HR ≥ 1.26 HR ≤ 0.79

HRs per standard deviation (SD) decrease estimated to be detected at 80% power calculated with the survSNP R package^75^ (https://cran.r-project.org/web/packages/survSNP/index.html) using the combined estimated sample size and death proportion from each cancer survival genome-wide association study (GWAS) and the respective Genomics England cancer survival GWAS, median survival and assuming a false positive rate of 0.05. Death proportion was defined as the proportion of cancer cases who died due to all-cause or cancer-specific mortality. Transformation of protein level measurements into normalised protein expression (NPX) units on a log₂ scale have been described previously.^43^

*Death proportion due to all-cause mortality.

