#### Sensitivity analyses

The main analyses will be repeated using genetic instruments constructed with more stringent thresholds: significance p value thresholds of < 5 × 10^−7^ and < 5 × 10^−8^, window sizes of 250 kb and 100 kb on either side of the gene of interest, and LD r^2^ thresholds of 0.2, 0.1 and 0.001. Although the primary analysis will only consider *cis* variants, *cis* and *trans* variants (> 500 kb from the gene of interest) will also be considered in secondary analyses. Instruments constructed from *cis* and *trans* variants will be selected based on p value and LD threshold (p < 5 × 10^−8^, r^2^ < 0.001) with reference to a random sample of 10 000 participants of European ancestry from the UK Biobank. Where instruments are constructed from two or more SNPs, the primary analysis will also be re-run iteratively excluding individual SNPs from instruments to investigate whether findings are driven by individual SNPs.^42^

Colocalisation analysis will be performed using Pair-Wise Conditional analysis and Colocalisation analysis (https://github.com/jwr-git/pwcoco) to investigate whether any significant MR results are biased due to LD between one variant causing a change in protein expression and another causing a change in cancer survival through an independent pathway.^4 55 64 65^

Pleiotropy will be investigated by conducting phenome-wide association studies to investigate whether the genetic instruments proxying PD-1 or PD-L1 expression are also associated with other phenotypes. This will be achieved using the IEU Open GWAS project (https://gwas.mrcieu.ac.uk/).^49 50^ The significance thresholds will be Bonferroni corrected for the number of traits looked up.^37 55^ Although these methods will not specifically investigate horizontal pleiotropy, they will assess the possible extent of either vertical pleiotropy or horizontal pleiotropy. Vertical pleiotropy occurs when there is a mediator in the pathway between the exposure and outcome and, in contrast to horizontal pleiotropy, does not violate MR assumptions.^38 42 51 64^

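### Leave-one-out on the r² < 0.30 cis instrument has limited ability to show that one variant drives a result, because LD tags of the very strong lead SNP can stay in when the lead is dropped

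*Protocol article*

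**What the plan says.** Under Genetic instrument selection, the primary cis instruments take SNPs in or within 500 kb of the gene at p < 5×10⁻⁶ and "at linkage disequilibrium (LD) r^2^ < 0.30". Under Estimator, an instrument of two or more SNPs is analysed by inverse-variance weighting, one SNP by the Wald ratio, and "Any LD between SNPs included in an instrument will be accounted for in analysis using a SNP correlation matrix". The same section plans a heterogeneity test across independent SNPs and a visual comparison of the SNP-level results.

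Under Sensitivity analyses, "the primary analysis will also be re-run iteratively excluding individual SNPs from instruments to investigate whether findings are driven by individual SNPs". The deletion scheme is thus attached to the primary analysis, that is, the r² < 0.30 set. The same section repeats the main analyses at "LD r^2^ thresholds of 0.2, 0.1 and 0.001" and at stricter p-value thresholds and narrower windows. It adds pair-wise conditional colocalisation and phenome-wide look-ups. It does not say that leave-one-out is repeated on the pruned instruments.

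Under Power, the lead PD-L1 SNP "explained approximately 4.17% of the variation in PD-L1 expression level"; the PD-1 figure is 2.97%.

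**The concern.** Leave-one-out is informative when the SNPs left behind carry information separate from the SNP removed. At r² up to 0.30 they may not. If a SNP is in the instrument only because it tags the lead, its protein and survival associations are both the lead's multiplied by the same correlation r, and its ratio equals the lead's. The correlation matrix corrects the weights and standard errors for LD. It does not take the deleted SNP's effect out of the marginal associations of the SNPs that remain.

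Suppose the survival signal at the locus comes from the lead variant by a route other than the protein. Dropping the lead may then return much the same estimate, and the stability could be taken as evidence that no single variant drives the finding. At stake is how a drug-repurposing signal resting on one variant is described.

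**Working it through.** **Inputs from the protocol article.** Protein GWAS N = 54 219 (Exposures). Lead-SNP R² = 0.0297 for PD-1 and 0.0417 for PD-L1 (Power). Deaths: breast 7769, lung 5190 (Table 2). Selection at p < 5×10⁻⁶ and r² < 0.30.

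**1. The plan's own figure.** The article gives no figure for leave-one-out; the nearest is Table 3. With HR = exp[(1.96 + 0.84)/√(R² × deaths)]:
- PD-L1, breast: exp[2.80/√(0.0417 × 7769)] = 1.168, stated 1.17.
- PD-L1, lung: exp[2.80/√(0.0417 × 5190)] = 1.21, stated 1.21; log HR 0.190.

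**2. How weak a tag is still selected?** Lead z² = N·R²/(1 − R²), which is 1660 for PD-1 (z = 40.7) and 2359 for PD-L1 (z = 48.6). A tag with no effect of its own has chi-square N·r²R²/(1 − r²R²). The 5×10⁻⁶ threshold is chi-square 20.8.
- Minimum r² = 20.8/[(N + 20.8)·R²] = 0.013 (PD-1) and 0.009 (PD-L1).
- At 5×10⁻⁸ (chi-square 29.7): 0.018 and 0.013.
- At r² = 0.30 the tag's chi-square is 487 (PD-1) or 687 (PD-L1). At r² = 0.001 it is 1.6 or 2.3 (p = 0.20 or 0.13), so it is not selected.

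Tightening p alone leaves tags in; pruning to r² < 0.001 removes them.

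**3. Only pure tags (assumed), one signal.** The expected estimate is the same with and without the lead. Expected z is multiplied by √J, where J is the joint r² of the remaining SNPs with the lead. Take a false signal of the size detectable with 80% power, so that z has mean 2.80 with the lead and √J × 2.80 without it, and the two z values correlate √J. Among results significant with the full instrument, the share still at p < 0.05 is:

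| J (assumed) | still p < 0.05 |
|---|---|
| 0.10 | 16% |
| 0.20 | 28% |
| 0.29 | 39% |
| 0.49 | 60% |

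**4. Companions with their own effect (assumed).** The true protein effect is 0, the lead's ratio is biased by log HR 0.20, and each of k companions has r² with the lead and an own effect worth a fraction w (0.1 to 0.5) of the lead's variance. Companions correlate with each other only through the lead. Correlated IVW gives
- all SNPs: 0.20/[1 + k·w(1 − r²)]
- lead dropped: 0.20·r/[r + √w(1 − r²)]

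Example, r² = 0.29, k = 1, w = 0.25: 0.20/1.1775 = 0.170, then 0.1077/0.8935 = 0.121, so 71% is retained.

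| r² with lead | retained, one companion | retained, three companions |
|---|---|---|
| 0.29 | 70–76% | 86–107% |
| 0.10 | 48–57% | 67–78% |
| 0.01 | 19–27% | 29–31% |
| 0.0009 | 6–10% | 10–11% |

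**5. Two signals (assumed).** PD-L1, lung: false log HR −0.190 at the lead, tags with J = 0.49, and an independent valid signal with R² = 0.005 and no survival effect.
- Full set: −0.190 × 0.0417/(0.0417 + 0.005) = −0.170
- Lead only dropped: −0.190 × 0.0204/(0.0204 + 0.005) = −0.153, where 0.0204 = 0.49 × 0.0417
- Pruned set (lead plus independent SNP), nothing dropped: −0.170
- Whole lead signal dropped: 0

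Only deletion of the whole signal shows the dependence.

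**The case against.** **The r² < 0.001 re-run removes every pure tag.** True by step 2. With one signal it reduces the instrument to one SNP and a Wald ratio, which already reveals that the result rests on one variant; the fix then adds only a caveat. With several signals the objection does not stand. Clumping keeps the most significant SNP, so the lead remains and the re-run does not test dependence on it (step 5).

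**Other checks are planned.** Heterogeneity is assessed across independent SNPs and SNP results are inspected by eye, which could help in the two-signal case, with perhaps limited power. Colocalisation is there "to investigate whether any significant MR results are biased due to LD between one variant causing a change in protein expression" and another variant causing a change in survival. If the same variant affects both, the signals can colocalise, so that check does not expose it. The article itself says that the phenome-wide look-ups do not specifically address horizontal pleiotropy.

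**The size depends on inputs the article does not give.** This stands. The number of SNPs and their LD are unknown, and 0.30 is an upper bound.

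**A condensed article may leave detail to the full plan.** The article does, however, state the deletion rule and the instrument to which it applies.

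A reader might infer that leave-one-out here cannot reveal a single driving variant. The figures do not support that. At low LD with companions that have their own effect, the estimate falls to a half or less. With pure tags at r² 0.29 and a false log HR of 0.20 (breast deaths), z falls from 3.60 to 1.94 with one tag and to 2.67 with three. That fall is hard to interpret, though, because losing a strong valid lead would also reduce precision.

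**Conclusion.** The point holds as a limit on what the check can show. On the protocol's own figures, the r² < 0.30 instrument can contain SNPs selected only because they tag the lead, and dropping the lead alone then leaves the expected estimate unchanged. The sizes in steps 3 to 5 rest on assumed LD, SNP counts and own effects: 16% to 60% of significant findings stay significant with pure tags, and retention of a false estimate ranges from about half (r² 0.10, one companion) to 70–107% (r² near 0.30), with less at lower LD.

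Two stronger inferences are not supported. The article does not say that a stable leave-one-out will be reported as proof against a single driving variant; it states only the question the check addresses. Nor does anything in it show that either lead variant is invalid. This is a modest defect in one sensitivity analysis and its interpretation, not in the main estimator.

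**What to change.** In Sensitivity analyses, add that leave-one-out will also be run on the r² < 0.001 (or a conditionally independent) instrument, or that each SNP will be deleted together with the instrument SNPs correlated with it in the UK Biobank reference sample. State that stability at r² < 0.30 will not be read as evidence against a single driving variant. Where only one independent signal exists, state that the finding rests on one variant and that leave-one-out offers no evidence of robustness.

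The cost is two or three sentences, since the pruned instruments and the correlation matrix are already planned. The downside is wider intervals after deletion, and no leave-out analysis for single-signal instruments.

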**Methods and analysis:**

We will use two-sample Mendelian randomisation to investigate the effect of genetically proxied levels of protein targets of two immune checkpoint inhibitors—programmed cell death protein 1 and programmed death ligand 1—on survival of seven cancer types (breast, colorectal, head and neck, lung, melanoma, ovarian and prostate). Summary genetic association data will be obtained from prior genome-wide association studies of circulating protein levels and cancer survival in populations of European ancestry. Various sensitivity analyses will be performed to examine the robustness of findings to potential violations of Mendelian randomisation assumptions, collider bias and the impact of alternative genetic instrument construction strategies. The impact of treatment history and tumour stage on the findings will also be investigated using summary-level and individual-level genetic data where available.

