Index event bias (also known as collider bias) may occur in studies of cancer survival if the hypothesised causal factor being evaluated for disease prognosis (in this case, PD-1 or PD-L1) is also a risk factor for disease onset.^4 37 66^ If SNPs found to be significantly associated with cancer survival are also associated with risk of the same cancer type, methods including the SlopeHunter R package (https://github.com/Osmahmoud/SlopeHunter) will be used to evaluate and account for index event bias.^67 68^

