### Study status

Based on reviewer feedback during peer review of this protocol, we have added methods to the protocol to evaluate the validity of constructed instruments, particularly with respect to potentially biologically relevant tissues other than blood,

Following submission of this protocol for publication, we have started to implement the analysis plan using breast, lung, melanoma, ovarian and prostate cancer survival as the outcomes of interest. We have also begun to perform sensitivity analyses detailed in this protocol, such as increasing the instrument construction criteria stringency and using cancer risk as the outcomes of interest, in addition to planned sub-group analyses for lung cancer survival across cancer stages. We anticipate completing these analyses in 2024 and submitting a paper detailing the findings of these analyses for publication by the end of 2024.

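### Index event bias is evaluated and corrected only after a significant survival result, so a survival estimate attenuated by that bias can go unexamined

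*Protocol article*

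**What the plan says.** The Sensitivity analyses section of the protocol article explains that index event bias may occur if the protein under study "is also a risk factor for disease onset". The next sentence sets the working rule: "If SNPs found to be significantly associated with cancer survival are also associated with risk of the same cancer type", methods including SlopeHunter "will be used to evaluate and account for index event bias". Two conditions must therefore both hold, one on survival and one on risk, before the bias is either assessed or corrected.

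Two other places bear on this. The abstract (Methods and analysis) promises robustness checks for "potential violations of Mendelian randomisation assumptions, collider bias and the impact of alternative genetic instrument construction strategies", with no significance condition. The Study status section reports that sensitivity analyses "using cancer risk as the outcomes of interest" have begun, but it does not connect them to a correction. No other section plans a correction that is free of the survival condition.

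**The concern.** The rule does not match the mechanism given one sentence before it. By the protocol's own account, the bias depends on an effect on onset. Adding survival significance makes the check one-sided. It can overturn a positive finding produced by selection, but it does not look at a finding that selection has pulled towards the null.

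The significance condition on colocalisation in the same section is a different matter. It asks whether a positive result is an artefact of linkage disequilibrium, which is a question about positive results only. Index event bias can move an estimate either way, so the same triage does not carry over.

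Non-significant results have some weight in this study. Under Aims and Positive controls, the cancers with approved indications serve as positive controls for the instruments and for the use of Mendelian randomisation in cancer survival. An attenuated result at such a site could be misread as a failure of instrument or method. The strengths and limitations list also concedes that survival sample sizes limit power, so the survival condition may often not be met.

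**Working it through.** **1. Reproduce the plan's power figure.** The Power section states "there is an estimated power of 80% to detect HRs of at least" 1.63 (or at most 0.62) across all seven cancers. The limiting case is melanoma with PD-1. Inputs: 1149 events (Table 2); the lead *PDCD1* SNP "explained approximately 2.97% of the variation in circulating PD-1 expression level"; Table 3 "assuming a false positive rate of 0.05", taken as two-sided because HRs are given in both directions.

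Approximation for a continuous genetic proxy: power = Φ(√(events × R²) × |ln HR| − 1.96).
- √(1149 × 0.0297) = √34.13 = 5.84
- 5.84 × ln 1.63 = 5.84 × 0.489 = 2.85
- Φ(2.85 − 1.96) = 81%, against 80% stated
- Smallest detectable HR: exp(2.80/5.84) = 1.615, against 1.63 stated

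The figure reproduces. Across Table 3, the computed upper HRs are within about 0.025 of those stated. No number in the plan is disputed here.

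**2. Size of the bias (assumed inputs; the documents give none).** Populations were simulated in which the protein and one other cause are independent. Only cases were kept, and the protein's log HR for survival was examined with the other cause omitted.
- Milder set: 4 million people, logistic selection, protein-risk OR 1.1 to 1.2 per SD, shared cause with OR 2 to 3 per SD for risk and the same log effect on survival. Bias in log HR: about -0.003 to -0.020, with simulation noise of about 0.001 to 0.004.
- Wider set: 6 million people, incidence about 5%, protein-risk OR about 1.1 to 1.35 per SD (or liability effects of 0.05 to 0.15), a strong other risk factor with log HR 0.5 for survival. Bias: about 0 to -0.04.

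**3. Effect on power, and so on the chance of passing a 5% survival test.** For a true effect at the detectable HR in Table 3, SE = ln HR / 2.80. With an attenuating bias b, power = Φ(2.80 − b/SE − 1.96).

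| Pair | HR (Table 3) | ln HR | SE | Power, b = 0.02 | Power, b = 0.04 |
|---|---|---|---|---|---|
| Breast PD-L1 | 1.17 | 0.157 | 0.056 | 69% | 55% |
| Ovarian PD-1 | 1.48 | 0.392 | 0.140 | 76% | 71% |
| Ovarian PD-L1 | 1.37 | 0.315 | 0.112 | 75% | 69% |
| Prostate PD-1 | 1.33 | 0.285 | 0.102 | 74% | 67% |
| Prostate PD-L1 | 1.26 | 0.231 | 0.082 | 73% | 64% |

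With no bias each entry is 80%. Breast PD-L1 has the smallest detectable effect of the 14 pairs, so it is the most sensitive to a given bias.

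**4. Direction.** Conditioning on being a case makes two causes of onset negatively correlated. If the protein raises risk and mortality and the other cause also raises both, the omitted cause pulls the protein's log HR down, towards the null. If the other cause raises risk but lowers mortality, the pull is away from the null.

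**The case against.** Several points on the other side stand.

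- **The risk analyses have begun.** Study status states no significance condition for them, so a risk signal might be seen even where survival is non-significant. This is partial mitigation. It does not close the gap, because the only correction rule is the one tied to survival significance.
- **The bias may be small.** This is fair. In the milder set it is about 2% to 11% of a log HR of 0.191 (HR 1.21), and the lower end of the wider set is about zero. The 55% pairs the largest simulated bias with the smallest detectable effect. A reader might go further and note that losing half the log HR would leave 29% power. For breast PD-L1 that needs a bias of 0.157/2 = 0.079, about twice the simulated maximum.
- **Direction is conditional.** Attenuation needs particular signs. An estimate pushed far enough past the null could become significant and meet the survival condition.
- **The simulations omit the shared cause entirely.** The Estimator section shows that the ovarian and prostate survival GWAS adjust for prognostic covariates. What that does to the bias was not examined.
- **The trigger is loosely specified.** The article gives neither its threshold nor whether it applies to single SNPs or to the MR estimate, so how often it would stay closed is unknown.

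**Conclusion.** The point holds as one of logic. Followed as written, the plan neither evaluates nor corrects index event bias for a non-significant survival result, although the cause it names does not depend on survival significance. An estimate attenuated by the bias can therefore go unexamined.

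The practical size cannot be known from the documents. The figures above rest on assumed risk effects and assumed shared causes of matching sign, and on true effects equal to the Table 3 values.

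A reader might infer that masked effects will be reported as null, or that non-significant ovarian and prostate results will be taken as evidence against repurposing. The article supports neither. It does not say how non-significant results will be worded, it calls the approved sites only crude positive controls, and it acknowledges limited power. Nor can it be said that every affected estimate is attenuated.

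**What to change.** Remove survival significance from the trigger. For every protein-cancer pair with available cancer-risk summary statistics:

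1. Report the MR estimate on risk beside the MR estimate on survival.
2. Report the survival estimate before and after index-event correction, as a sensitivity analysis, whatever the survival p value. At minimum, do this wherever there is evidence of an association with risk.

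The uncorrected estimate stays in view, so nothing is lost from the main analysis. The cost is a few more runs, some of which may overlap with the risk analyses already begun, and wider intervals for corrected estimates. It also depends on suitable risk data for each site. The article lists no risk sources, and Study status names five of the seven cancers as started, so any pair that cannot be corrected should be named.
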